#### School recruitment and randomization

2.4.1

In Phase I, a convenience sample of approximately 50 students will be recruited. A call to action will be used to engage adolescents through the development of infographics and information about the aims of this phase, which will be disseminated through social media, personal contacts, or emails. Since these tests will be conducted outside the school timetable, no schools will be directly contacted. Instead, parents or legal guardians will be responsible for contacting the research team if their children are interested in participating in the study and they provide their consent. In this call to action, incentives, such as activity wristbands will be given away to participating adolescents. For Phase II, a specific selection protocol will be implemented through a random draw. A list of all public secondary schools in each of the participating cities of the government educational institutions in Andalucía will be obtained. The schools in the three cities (Granada, Almería, Jaén) will be contacted by phone, and if they are interested in participating, they will have to meet a series of inclusion and exclusion criteria presented in Table 1. During the call, a meeting will be arranged with interested schools to explain to the management team and teaching staff the main objective of the study, as well as to obtain official consent to participate in the project from the school. After that, the research staff with the help of Physical Education teachers will recruit participants and their families, by visiting selected classes and explaining the study to prospective adolescent participants and finally requesting the family’s consent. The inclusion and exclusion criteria for the participants are presented in Table 2. To complete the sample of students in the intervention group, several schools may be needed, as not all students will be able to participate in the school-based cycling intervention due to family reasons, distance, predisposition, etc. To encourage as many students as possible from the intervention school to participate (with their families’ consent) in the school-based cycling intervention, an incentive system will be planned similar to other studies (42, 43). This incentive will consist of a voucher to be redeemed for sports equipment, provided that the participant has completed the 8 weeks of intervention and presents valid data at both baseline and follow-up. Once finished the baseline assessment, the participating schools will be randomly assigned through a draw to either a control or experimental group.

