
**Table 1 tab1:** Schools’ inclusion and exclusion criteria.

Inclusion criteria	Exclusion criteria
The school has a specific space for parking bicycles and allows their parking	The school does not have specific infrastructure to park or store bicycles
The school has at least two classes per grade	The school offers bus transportation to the adolescents
At least eight students from the school will agree to participate in the study	The school is already participating in other interventions focused on promoting healthy behaviors
Schools from urban areas	The school has implemented an intervention to encourage commuting to school within the last year
	Schools from rural areas

**Table 2 tab2:** Participants’ inclusion and exclusion criteria.

Inclusion criteria	Exclusion criteria
Adolescents’ females and males aged from 12 to 17 years old (both ages included)	Adolescents younger than 12 years or older than 17 years
Healthy participants who can ride a bicycle safely and without difficulty.	Participants with any injury or medical condition that prevents safe participation in cycling to and from school
Be able to cycle to and from school at least 3 days per week during eight consecutive weeks (Intervention group)	Insufficient ability to ride a bicycle or inability to cycle to and from school at least 3 days a week (Intervention group)
Not to cycle to and from school more than 3 days a week during the last year	Participants who have cycled to and from school more than 3 days a week during the past year
To present a valid signed consent from their parents or legal guardians	Participants without a valid, signed parental or guardian consent form
To present valid data at baseline and follow-up from all the outcomes assessed	Participants who do not provide valid data for all assessed outcomes at baseline and follow-up

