### School-based cycling intervention program

2.8

The school cycling intervention program will include 1 week of training and familiarization with the bicycle using the *Bikeability* methodology (88), and the adolescents’ commuting to and from the school for 8 weeks with the support of encouragement strategies during the intervention. *Bikeability* sessions will have the objective of familiarizing the students with cycling to and from school. This is based on the fact that participants will know how to cycle, but many of them might not have cycled for a long time and have not cycled regularly. Moreover, *Bikeability* sessions will help the research staff to analyze if any student does not have sufficient capacity to carry out the intervention. The *Bikeability* methodology, previously tested and published as innovative material by our research group (88), will consist of two sessions over a one-week period delivered by the research group with the support of the Physical Education teacher during Physical Education class to acquire practical skills and understand how to cycle safely and effectively. The components and content of these two sessions focus on: (i) knowledge about road safety regulations, safety equipment for cyclists, hand signals while cycling, and the benefits of cycling as a means of transportation, and (ii) cycling-related skills. Prior to the first session, the Physical Education teacher will provide students with educational theoretical material to raise awareness about the benefits and usefulness of cycling as a mode of travel, knowledge about road safety rules for cyclists, knowledge about safety equipment for cyclists for both the cyclist and the bicycle, and hand signals while cycling in an urban context. The sessions conducted by the research group with the support of the Physical Education teacher are described below:

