#### Analysis populations

2.10.1

In the ENERGYCO project, per-protocol and intention-to-treat (ITT) approaches, as well as sensitivity analyses, will be conducted. On one hand, the per-protocol approach will be used to present the main and secondary analysis. Participants from the intervention group who have cycled to and/or from school at least 3 days/week over 8 weeks will be included. Additionally, participants from both the intervention and control groups must have valid data at baseline and follow-up for the outcomes of interest (e.g., RMR and PAEE). On the other hand, the ITT approach will be used to present main and secondary analysis, but in the Supplementary material. This approach will include all participants in both the intervention and control groups who have valid data at baseline and follow-up or who have missing data at either baseline or follow-up. Finally, the potential impact of missing data will be assessed using various imputation models and sensitivity analyses. Specifically, we will conduct sensitivity analyses to determine whether the choice of imputation method affects the results. Additionally, no interim analyses will be performed.

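### Table 2 makes eligibility depend on follow-up data and, for one arm only, on being able to cycle: neither rule can be enforced before the draw, and the first contradicts the ITT definition

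*Protocol article*

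**What the plan says.** Table 2 (section 2.4.1) sets participant eligibility. Two of its rows concern data completeness. The inclusion column has "To present valid data at baseline and follow-up from all the outcomes assessed", and the exclusion column mirrors it with "Participants who do not provide valid data for all assessed outcomes at baseline and follow-up".

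Two further rows carry an arm label. The inclusion is "Be able to cycle to and from school at least 3 days per week during eight consecutive weeks (Intervention group" and the matching exclusion is "Insufficient ability to ride a bicycle or inability to cycle to and from school at least 3 days a week (Intervention group". The other rows (age, safe riding and health, recent cycling habit, consent) carry no arm label.

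On timing, section 2.4.1 says: "Once finished the baseline assessment, the participating schools will be randomly assigned through a draw". Allocation is therefore unknown at recruitment, consent and baseline.

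Section 2.10.1 defines the ITT set as all participants in both groups, including those "who have missing data at either baseline or follow-up", and plans several imputation models with sensitivity analyses. The per-protocol set, used for the main presentation, needs valid data only for the outcomes of interest. ITT results go to the supplement.

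**The concern.** Eligibility should be decidable before allocation and the same in both arms. Here one criterion depends on an event some eight weeks after the draw, and another applies to a group that does not exist until the draw has been made.

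Two things are at stake. First, ITT is the plan's safeguard against its per-protocol main analysis. If Table 2 governs who counts as a participant, that safeguard becomes a complete-case analysis. Second, adolescents who cannot sustain cycling to school could be removed from the intervention arm while their counterparts stay among the controls. Such adolescents plausibly differ in fitness, activity and body composition, and in how these change. Adjusting for the baseline value of the outcome does not guarantee that the difference disappears.

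**Working it through.** **1. Order of events.** Section 2.4.1 gives recruitment and consent, then baseline, then the draw; the intervention and follow-up come after.
- Valid follow-up data on all outcomes: decidable only after follow-up, hence after the draw.
- Ability to cycle 3 days a week, intervention group only: it could be assessed before the draw, but it cannot be applied to that group alone until the draw has been made.

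**2. Table 2 against section 2.10.1.** An adolescent with a missing follow-up value is ineligible under Table 2 and belongs to ITT under section 2.10.1. Both cannot hold. Table 2 is even stricter than the per-protocol set, because it asks for all outcomes rather than those of interest. Read literally, controls could not satisfy it. Cycling skills are scored during the Bikeability session (section 2.7.2.15), and control schools are offered those sessions only after the eight weeks (section 2.5).

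**3. The plan's own loss figure.** Section 2.4.2 needs 250 and assumes about 15% dropout: 250 / (1 − 0.15) = 294.1, so 295, which agrees with its target of about 300. It states the 15% for the experimental group only. With 50 per arm in each of three cities there are 150 per arm, and 150 × 0.15 = 22.5, so about 22 adolescents. That leaves about 127.5 against 150, or 277.5 in all. This is still above 250, so at this rate the problem is one-sidedness rather than numbers.

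**4. Loss under the all-outcomes rule.** The documents give no validity rates, so these are assumed. Two patterns bracket the loss:
- Missingness follows sessions: three assessment days (section 2.6.1) × 2 visits = 6 session-visits, kept = p^6.
- Missingness independent by measure: 15 Phase II measures (Table 3 lists more) × 2 visits = 30, kept = p^30.

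| Assumed validity p | p^6 (of 300) | p^30 (of 300) |
|---|---|---|
| 0.99 | 94% (282) | 74% (222) |
| 0.98 | 89% (266) | 55% (164) |
| 0.95 | 74% (221) | 21% (64) |

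At 98% the loss is about 11% or about 45%, depending on the pattern.

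**5. Illustrative bias.** Suppose 15% of one arm is removed and retention correlates r with the adjusted outcome (normal model). The shift is r × φ(z)/(1 − 0.15), with z the 15th percentile of the standard normal; the multiplier is about 0.274. For r = 0.1, 0.3 and 0.5 the shift is 0.03, 0.08 and 0.14 SD. The correlations are assumed.

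**The case against.** The best defence is that section 2.10.1 shows what the investigators intend: adolescents with missing data stay in ITT, gaps are imputed, and per-protocol completeness is judged by outcome. On that view the Table 2 rows are loose drafting. The intention is credible, but the article states both rules without saying which prevails.

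Several stronger readings might be inferred and are not supported:
- *ITT would be empty.* It would be a complete-case set, not a set without members.
- *Controls would be unselected.* Safe riding ability, the health exclusion and complete data apply to both arms. Only the 3-days-a-week criterion is one-sided.
- *Bikeability removes weak cyclists.* Section 2.8 says only that the sessions "help the research staff to analyze if any student does not have sufficient capacity to carry out the intervention". It does not say that such adolescents leave the trial or the analysis.
- *Schools are recruited towards a known arm.* Section 2.4.1 says "To complete the sample of students in the intervention group, several schools may be needed", which is ambiguous. Section 2.4.2 speaks of adding schools to reach 100 adolescents per city, the total for both arms. No text adds a school to one arm after the draw.
- *Nearly half the sample would be lost.* That needs independence across 30 measure-visits. Most measures are grouped into three assessment days, resting metabolic rate also has an equation-based estimate (section 2.7.1.1), and accelerometer non-wear is imputed (section 2.7.2.5). All of these soften the loss.

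**Conclusion.** The point holds. Table 2 is wrong as written in two respects: it conditions eligibility on follow-up data, which contradicts the ITT definition, and it attaches a feasibility criterion to one arm although arms are unknown until after baseline. If applied, it reduces ITT to complete cases and permits exclusion after randomisation in the intervention arm alone.

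These conclusions rest on the text and need no assumed figure. The size of the loss and of any bias cannot be computed from the documents; the 11% to 45% range is conditional on 98% validity and on the missingness pattern. The only loss figure that the plan supplies is its own expectation of about 15% in the experimental arm, roughly 22 of 150.

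**What to change.** 1. Delete the two valid-data rows from Table 2. State completeness outcome by outcome in the section 2.10.1 analysis sets. Do not replace the rows with a required baseline primary outcome, since section 2.10.1 keeps adolescents whose baseline is missing.
2. Remove the arm label from the 3-days-a-week rows and assess that criterion identically in every adolescent at enrolment, before the draw.
3. State that every adolescent enrolled before the draw in a randomised school stays in ITT as allocated, including anyone later found unable to cycle.
4. Clarify in section 2.4.1 that recruitment and baseline in a city are complete before its schools are drawn, and that no school is added to one arm afterwards.

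The cost is protocol wording, plus somewhat slower control recruitment because all adolescents must meet the same cycling criterion. The change is needed before the draw, because exclusions made after it cannot be repaired in the analysis.

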#### Sample size calculations

2.4.2

For Phase II, at least 250 participants are needed to ensure an acceptable sample size, assuming 5% precision (*α* err prob) and a very high statistical power of 95%. (Error 1-*β* err prob) (44). This calculation has been made considering a study objective where the effect of the intervention program on the different health variables of young people is evaluated (e.g., RMR, EE, PA levels, body composition, muscle strength). In this study there will be two main comparison groups (experimental group and control group) and for this the ANCOVA statistical analysis will be performed: fixed effects, main effects, and interactions (F test) and with an effect size = 0.25. It is assumed that there will be dropouts during the school-based cycling intervention (≈15% in the experimental group), so ≈300 adolescents will be recruited from different schools in the three Spanish cities. Following the forecasts in Figure 1, 100 adolescents would be needed in each city. The groups randomization will be done at a 1:1 ratio at city level (i.e., from each city, 50 participants will be randomized to intervention and 50 to control groups), as other studies have done before (45). Nevertheless, due to the low prevalence of cycling to school in Spain (46), we will try to recruit as many schools as necessary in each city to reach the number of 100 adolescents.

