### Study design and participants

2.1

The ENERGYCO study is a cluster randomized controlled trial to be conducted in high schools from three Spanish cities (Granada, Jaén, and Almería), where the schools will be the units of randomization, and individuals within the schools will be the units of analysis (participants). This project will consist of two main phases: Phase I will present a cross-sectional design which will take place before starting the Phase II. A cross-sectional approach will be adopted due to its suitability for capturing a snapshot of key variables of interest at a specific point in time, aligning with the objectives of this phase (i.e., comparing PAEE associated with different modes of commuting to school and developing predictive equations for measuring PAEE in Phase II). In contrast, for Phase II a cluster parallel-arm design will be employed to allocate interventions effectively to larger groups while accounting for potential intra-cluster variability, enhancing the external validity and generalizability of the results. The ENERGYCO study has been approved by the Review Committee for Research Involving Human Subjects at the University of Granada (Reference: 2496/CEIH/2021) and registered with a ClinicalTrials.gov ID: NCT06414668. In addition, the present study protocol has been written in accordance with the Standard Protocol Items: Recommendations for Interventional Trials (SPIRIT) statement (See Supplementary material 1).

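### The 95% power claimed for 250 adolescents makes no allowance for randomising schools, so it is not shown, and it falls short unless the ICC and the number of students per school are both small

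*Protocol article*

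**What the plan says.** All references are to the protocol article.

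- **Design (section 2.1).** Schools are the units of randomisation and adolescents the units of analysis. The cluster design is presented as "accounting for potential intra-cluster variability".
- **Sample size (section 2.4.2).** The text states that "at least 250 participants are needed to ensure an acceptable sample size", "assuming 5% precision" for alpha and "a very high statistical power of 95" per cent. It says "there will be two main comparison groups (experimental group and control group"), and names the test as ANCOVA, "fixed effects, main effects, and interactions (F test) and with an effect size = 0.25".
- **Inflation (section 2.4.2).** About 15% dropout, stated for the experimental group, takes the target to about 300: 100 per city, 50 per arm. The section describes participants being randomised to arms within each city, although schools are what is randomised. It leaves the number of schools per city open until 100 adolescents are reached.
- **School criteria (Table 1).** "At least eight students from the school will agree to participate in the study" sets a minimum. No maximum is given.
- **Analysis (sections 2.10.1 and 2.10.2).** The main presentation is per-protocol. The model is ANCOVA with group as fixed factor, the baseline value and school-level covariates.

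**The concern.** Adolescents in one school share teachers, routes, infrastructure and the delivery of the intervention, so their outcomes are likely to be correlated. When whole schools are allocated, that correlation inflates the variance of the group difference by the design effect. The degrees of freedom for the comparison also come from the number of schools, not the number of adolescents. A calculation that treats 250 adolescents as independent therefore overstates power by an amount that depends on the ICC and on how many students each school contributes.

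The article states its method, inputs, result and inflation. Together these show that clustering did not enter the figure, so this is more than detail left to a fuller document. At stake is the power claim itself. Recruitment stops at 100 adolescents per city, and that target could be met by many small school groups or by a few large ones. The headcount is the same in both cases, but the power is very different.

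**Working it through.** **1. Reproducing the plan's figure.** Inputs from section 2.4.2: alpha 0.05, power 0.95, effect size 0.25 (read as Cohen's f, which is d = 0.5 for two equal groups) and an ANCOVA F test. Power comes from the noncentral F distribution with noncentrality λ = N × f² = N × 0.0625 and denominator degrees of freedom N − groups − covariates.

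- Numerator df 1 (two-group main effect): power is 94.9% at N = 209 and 95.0% at N = 210, so **N = 210**. At N = 250 power is 97.6%.
- Numerator df 2: power is 94.99% at N = 250 and 95.07% at N = 251, so **N = 251**.

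The required N is unchanged by using 0 to 10 covariates. So 250 is reproducible, but with 2 numerator df and not with the 1 df of the two-group comparison that the section describes. Two df would fit, for example, a group-by-city interaction: (2 − 1) × (3 − 1) = 2.

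**2. Inflation.** 250 / 0.85 = 294, which is about 300. Dropout accounts for the whole step from 250 to 300, leaving no separate design effect.

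**3. Adding clustering.** The article gives no ICC and no average number of students per school, so the values below are assumptions: ICC 0.01 to 0.10 and m = 8, 10 or 25 analysed per school. The value 8 is taken from the Table 1 minimum.

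- Design effect: DE = 1 + (m − 1) × ICC
- Effective sample size: 250 / DE
- Noncentrality: 0.5 × √(250 / (4 × DE))
- Reference distribution: t with (250 / m − 2) df, two-sided 5%

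Worked example, m = 25 and ICC = 0.05: DE = 1 + 24 × 0.05 = 2.20. The effective size is 250 / 2.20 = 114, the noncentrality is 0.5 × √(250 / 8.8) = 2.67, and with 10 − 2 = 8 df the power is 65%.

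| Students per school (schools) | ICC 0.01 | ICC 0.02 | ICC 0.05 | ICC 0.10 |
|---|---|---|---|---|
| 8 (about 31) | 96% | 95% | 91% | 83% |
| 10 (25) | 95% | 94% | 88% | 78% |
| 25 (10) | 87% | 81% | 65% | 47% |

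**4. Where 95% survives.** The two-group test needs 210, so 250 can absorb a design effect of up to 250 / 210 = 1.19. Ignoring the loss of degrees of freedom, that means an ICC no larger than 0.19 / (m − 1): about 0.027 at m = 8, 0.021 at m = 10 and 0.008 at m = 25. Using schools − 2 df tightens these limits.

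**The case against.** The strongest reply is that the article does not give what is needed to show a shortfall. That is right. A reader might infer that the design fails to reach 95% power, but the documents do not support so firm a statement. With 8 to 10 students per school and an ICC of 0.01 to 0.02, 250 analysed still gives about 94 to 96%. Low cycling prevalence and the plan to use as many schools as necessary point towards smaller school groups. Figure 1 is not shown and may carry expected school numbers, so their absence cannot be asserted.

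A reader might also infer that 250 is an arithmetic error, or that it must come from a three-group calculation. Neither holds. The named routine covers interactions as well as main effects, and a two-group by three-city interaction has 2 df and gives 251. The gap between 210 and 250 enlarges the sample.

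There may also be some slack. If the 15% applies only to the experimental arm, 300 recruited leaves 150 × 0.85 + 150 = 277.5 analysed. With 277, power is about 96% for schools of 10 at ICC 0.02, but about 67% for 10 schools at ICC 0.05. The slack helps small clusters and does not rescue large ones. Against it, section 2.10.1 also removes intervention participants who cycle on too few days and anyone without valid data at both visits. The article does not say whether the 15% covers them.

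Baseline adjustment may recover some precision, but section 2.4.2 states no baseline correlation.

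Finally, the article nowhere says that a null result would be read as no effect, and it lists a possibly small sample among its limitations. No such misuse should be attributed to it.

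**Conclusion.** The point stands in this form: the 95% rests on independence between adolescents, which the randomisation of schools contradicts, and nothing in the stated calculation allows for it. The 95% is therefore not shown. It falls short unless the ICC and the students per school are both small. Over the assumed range, power at 250 analysed runs from about 96% (8 per school, ICC 0.01) to 47% (25 per school, ICC 0.10). These figures assume d = 0.5, equal school sizes, schools minus 2 degrees of freedom and ICC values that are not from the documents.

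The unstated numerator degrees of freedom are a secondary reporting point and not a shortfall.

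**What to change.** In section 2.4.2, replace the unqualified 95% with the power that 300 recruited adolescents give in the main per-protocol population, calculated as a cluster trial for RMR. State:

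- the assumed ICC, its basis and a range around it;
- the expected students per school and schools per arm;
- the design effect 1 + (m − 1) × ICC, with schools minus 2 degrees of freedom;
- the effect-size metric and the numerator degrees of freedom (1 for the two-group comparison, which gives 210 before clustering, or the reason for 2);
- which losses the 15% covers (dropout alone, or also non-adherence and incomplete data) and in which arm.

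Describe schools, not participants, as what is randomised within each city.

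The cost is a recalculation and a revised paragraph. Restating the power needs no added participants, but it does not restore 95% where the ICC or school groups are large. Where recruitment allows, spreading the fixed 300 over more schools raises power, at some logistical cost. The minimum of eight students per school limits this to about 37 schools (300 / 8 = 37.5).
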